### Intervention

The four conditions will comprise receipt of a given quantity of a carbonated cola sugar-sweetened beverage (SSB), sub-divided into bottles of one of four different sizes:i.1500 ml bottles,ii.1000 ml bottles,iii.500 ml bottles andiv.250 ml bottles.

In any 1-week, households will receive their preference of cola (Coca-Cola**®** or Pepsi Cola**®**) in just one size of bottle, with the number of bottles being determined by the total volume of cola each household receives, which will be fixed across all four intervention periods. This fixed volume will be determined with reference to the volume of cola households purchased during a 2-week baseline period, as assessed by till receipts and by self-report, rounded up to the nearest multiple of 3 l. For example, if households purchased 2 l per week, they will receive 3 l during each intervention period; if they purchased three and a half litres, they will receive 6 l etc. Households purchasing amounts already consisting of a multiple of 3 l will receive this exact amount (e.g. if they purchased 3 l, they will receive 3 l). Volumes consisting of multiples of 3 l are needed to avoid the total quantity varying systematically between intervention periods, thereby confounding the effect of altering the bottle size with volume. During each intervention week, households will be given the opportunity to receive additional deliveries should they want these.

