All participating households will receive all interventions according to a pre-specified random order (see ‘Randomisation’ section for details). During the first intervention period, four households will receive cola in each of the intervention bottle sizes, subsequently crossing-over to the other conditions during the remaining three intervention periods, until all households have been exposed to all conditions. All intervention periods will be conducted during school term times, in order to avoid increased consumption during any specific period due to the increased presence of children in the homes. During the intervention periods, a researcher will visit participating households to deliver the total volume of the cola (Coca-Cola**®** or Pepsi Cola**®** depending on their preference) SSB for the forthcoming week. The researcher will remove any existing SSB products that are in the household, with financial compensation provided for any removals. At the end of each week, households will be requested to pay for the SSB drinks they consume at their usual purchasing rate. During the intervention periods, households will be requested to continue to keep all bottles whether the contents are consumed, partially consumed or not consumed. They will be told that the reason for this is to accurately estimate how much they need to pay for their drinks, based on the amount they consumed.

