### Baseline assessments

At enrolment, household representatives (i.e. individuals who are recruited from each household to provide the necessary data) will be asked to give written informed consent on behalf of their household for participating in the study and for adhering to the study procedures. Following this, they will be requested to complete a questionnaire to record their household’s demographic characteristics, including the number of adults and children living in their home, their age, gender, highest educational qualification and annual household income. They will also be asked to indicate how much cola per week their household usually buys for in-home consumption, as well as the total amount their household drinks outside the home. The amount of cola typically consumed per week by each household will also be estimated based on grocery shopping till receipts, which household representatives will be asked to collect during a 2-week period. Discrepancies between amounts indicated by till receipts and self-report will be discussed with household representatives, in order to determine the household’s typical weekly consumption as accurately as possible.

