### Follow-up assessments

At the end of each of the intervention weeks, household representatives will be asked to estimate the amount of SSB their household consumed in the preceding week and to indicate whether any SSB was consumed by non-household members (i.e. visitors). To build credibility for the cover story they will also be asked to rate their consumption experiences, as well as the experience of any visitors they might have had, who consumed part of their SSB stock.

In order to determine whether households believed the cover story or were aware of the purpose of the intervention and of the study’s aim, at the final follow-up assessment, they will be requested to state what they thought the study was about. Awareness of the study’s aim will also be assessed during interviews with household representatives, which will be conducted after the end of all intervention periods. Household representatives will be fully debriefed on the study aims at the end of this final assessment session. The debriefing process will include an explanation of the study’s scientific aim and the reasons for not revealing this at recruitment (i.e. that awareness of the intervention’s purpose was expected to influence the outcome), as well as information regarding the adverse consequences of excessive SSB consumption. This information will be provided both verbally by a member of the research team, as well as in writing. At this point, household representatives will be given the opportunity to make any enquiries regarding the study and address any related issues they might have. They will also be asked to provide written consent for their household’s collected data to be used having been informed of the scientific aims of the study.

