### Data analysis

The main analysis of this study will include descriptive statistics of feasibility and acceptability outcomes, including recruitment and attrition rates. We will also calculate the average change from baseline in SSB consumption during each intervention period to estimate possible effect sizes from which to power the main trial.

Analysis of the anonymised data gathered through the semi-structured interviews will be conducted following the principles of the Framework method [41].

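### Drinks of every sugar-sweetened kind are removed but baseline is cola only, so the change from baseline in SSB consumption meant to power the main trial is either unmatched or open to switching

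*Protocol article*

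**What the plan says.** The product scope changes from one stage of the study to the next.

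- **Removal (Intervention):** "The researcher will remove any existing SSB products that are in the household". This covers every SSB in the home, not only cola.
- **Supply (Intervention):** the researcher visits to "deliver the total volume of the cola" for the coming week. On its size: "This fixed volume will be determined with reference to the volume of cola households purchased during a 2-week baseline period". The volume is rounded up to a multiple of 3 l, and extra deliveries are available on request.
- **Baseline (Baseline assessments):** the representative is asked to "indicate how much cola per week their household usually buys for in-home consumption". On the receipts: "The amount of cola typically consumed per week by each household will also be estimated based on grocery shopping till receipts". Out-of-home drinking is asked about as well, but no in-home volume of other SSBs is mentioned.
- **Weekly self-report (Follow-up assessments):** the representative is asked to "estimate the amount of SSB their household consumed in the preceding week".
- **Listed outcome (Outcomes and measures):** millilitres of cola per intervention week, measured from the bottles and by self-report.
- **Analysis (Data analysis):** the team will "calculate the average change from baseline in SSB consumption during each intervention period", and the result is to supply effect sizes for powering the main trial. Objective vii under Aim and objectives gives the same purpose.

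**The concern.** The one effect estimate that the article names is a difference between two quantities that may not be alike. There are two readings of SSB in the Data analysis section.

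1. **All SSBs.** The removal sentence uses the term in this wide sense. On this reading the follow-up quantity has no described counterpart at baseline.
2. **The study cola.** A baseline then exists, but it was taken while other SSBs could be in the home. The intervention weeks come after those stocks are removed and cola is delivered. Cola drunk in place of the removed drinks counts as a change from baseline although bottle size did not cause it.

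At stake is the effect size carried into the sample size of the main trial. A second consequence concerns the assessment procedures. The outcome list treats bottle counts and self-report as two measures of the same cola volume. A weekly question worded as SSB could draw a larger answer from a household that also drinks other SSBs, and the two measures would then disagree for a reason unrelated to accuracy.

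**Working it through.** **Figures the article gives.** There is no power, effect or variance figure to reproduce. The design figures do reproduce: 4 sizes × 4 households per cell = 16 households. Rounding up to a multiple of 3 l gives 2 l → 3 l, 3 l → 3 l and 3.5 l → 6 l, as in the Intervention section.

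**Model.** Let *s* be a household's baseline weekly litres of SSBs other than cola, *q* the share of *s* replaced by cola after removal, and *e* the true effect of a bottle size on weekly cola volume relative to baseline. If effects add:

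- change from cola baseline = *e* + *s*·*q*
- contrast with 1500 ml = (*e* + *s*·*q*) − (*e*₁₅₀₀ + *s*·*q*) = *e* − *e*₁₅₀₀

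**Inputs.** The article gives no value for *s*, *q* or *e*. The following are assumptions for illustration: cola baseline 3 l a week, and *e* = 0, −0.15, −0.30 and −0.45 l for 1500, 1000, 500 and 250 ml. The switched volume *s*·*q* is set at 0, 0.5 and 1 l. For example, half of 1 l gives 0.5 l and half of 2 l gives 1 l.

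| Switched volume | 1500 ml | 1000 ml | 500 ml | 250 ml | 250 minus 1500 ml |
|---|---|---|---|---|---|
| 0 l | 0 | −0.15 | −0.30 | −0.45 | −0.45 |
| 0.5 l | +0.50 | +0.35 | +0.20 | +0.05 | −0.45 |
| 1 l | +1.00 | +0.85 | +0.70 | +0.55 | −0.45 |

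The first four columns after the switched volume are changes from baseline in litres per week. With 0.5 l switched, the 250 ml figure is −0.45 + 0.5 = +0.05 l, so a reduction reads as a small increase. Relative to the 3 l baseline the shift is 0.5/3 = 17%, or 1/3 = 33% with 1 l switched. The last column does not move.

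**If the size effect is proportional.** Take −15% for 250 ml, applied to baseline plus switched volume. The contrast with 1500 ml is then:

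- no switching: −0.15 × 3 = −0.45 l
- 0.5 l: −0.15 × 3.5 = −0.525 l
- 1 l: −0.15 × 4 = −0.60 l

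The contrast in litres grows somewhat, while the percentage contrast stays at −15%. The change from baseline for 250 ml still moves a great deal: 0.85 × 3.5 − 3 = −0.025 l with 0.5 l switched, and 0.85 × 4 − 3 = +0.40 l with 1 l switched.

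**The case against.** The strongest reply is that the study is a within-household crossover. Every household receives all four sizes, and removal and cola-only supply are the same under each. Subtracting one period's change from another's removes the baseline and the common shift. This stands, and the working confirms it. It does not rescue the stated analysis, because the Data analysis section names the change from baseline, not the difference between sizes, as the source of effect sizes.

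A second reply is that the article often uses SSB for the delivered cola (Design, Intervention) and that the outcome list is in cola, so a matching baseline exists. That is a fair reading. It answers the missing baseline but leaves the exposure to switching.

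A third is that a journal article condenses, and receipt coding may be set out in the full protocol. If other SSBs are already coded there, part of the remedy is in place. The point here rests on what the article states, which is that the receipts are used to estimate cola.

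A reader might infer three stronger things that the documents do not support.

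- **That switching is forced.** Existing stock is removed, with compensation, but no ban on buying other SSBs is stated.
- **That supply runs out under every size and flattens the differences.** Additional deliveries are offered each week, and rounding up leaves 3 − 2 = 1 l and 6 − 3.5 = 2.5 l to spare in two of the article's own examples. Flattening would need a household with no slack that asks for nothing more.
- **That the comparison of bottle sizes is biased.** A shift common to all four weeks cancels, exactly if additive and in percentage terms if proportional.

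**Conclusion.** The mismatch of scope is in the text and affects the one effect estimate that the article specifies. Under the wide reading of SSB, the change from baseline has no described baseline to match. Under the narrow reading, it mixes the effect of the study bottles with any switching from removed drinks, by the same *s*·*q* litres in each period if effects add. The direction is upward, so a reduction would be understated, hidden or reversed in the change-from-baseline figure.

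The size cannot be computed from the documents. The 0.05 l, 17% and 33% figures rest on assumed volumes of other SSBs, assumed replacement and assumed size effects. If few households keep other SSBs, or if they simply buy them again, the shift is small. The contrast between bottle sizes is largely sound. This is therefore a fault in the chosen estimate and its terminology, not in the crossover design. It should be corrected because this study exists to settle the assessment procedures and the effect size for the larger trial.

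**What to change.** 1. Use one product scope in Follow-up assessments, Outcomes and measures, and Data analysis. Where the study cola is meant, write cola. Where all SSBs are meant, say so.
2. From the till receipts already being collected, also extract the weekly volume of other SSBs, and add a matching item to the baseline questionnaire. Word the weekly question so that cola and other SSBs are reported separately.
3. Compare cola with cola and all SSB with all SSB.
4. Take the within-household difference in cola volume between bottle sizes as the effect estimate for the main trial. Keep the change from baseline in each period, labelled as descriptive, with a note that it may include switching.

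The cost is one extra column in receipt coding, one baseline questionnaire item and a rewording of the weekly question. No extra visits are needed. One limit remains: at follow-up, other SSBs would be known from self-report only, since the bottle measure covers cola.

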### Randomisation

Randomisation will be restricted to ensure that (a) equal numbers of households receive each of the four bottles sizes at each intervention period (Table 1) and (b) each bottle size is equally likely to be preceded and followed by each other bottle size. These conditions are imposed to ensure that the order in which the interventions are presented is counterbalanced and that outcomes are not affected by potential order and carry-over effects. In a larger trial, such as the future one we are planning, we do not foresee the need for imposing such restrictions, as randomisation of a large number of households is expected to minimise the chance of imbalances in the order of the interventions.

**Table 1 Tab1:** Number of households allocated to each bottle size during each intervention period

	Bottle size			
	250 ml	500 ml	1000 ml	1500 ml
Intervention period 1	*n* = 4	*n* = 4	*n* = 4	*n* = 4
Intervention period 2	*n* = 4	*n* = 4	*n* = 4	*n* = 4
Intervention period 3	*n* = 4	*n* = 4	*n* = 4	*n* = 4
Intervention period 4	*n* = 4	*n* = 4	*n* = 4	*n* = 4

We will initially randomly select four sequences (out of 24 available sequences) dictating the order in which households receive each bottle size. These four sequences will then be used to determine the other 12 sequences needed to balance the initial allocations to ensure that the aforementioned conditions are met. Each household will be randomly allocated to one of these 16 sequences. In this manner, the order in which each household receives each bottle size will be pre-specified at the start of the study. The randomisations will be determined during the run-in period (see ‘Procedure’ section) by a statistician independent from the research team, with the assistance of computer software.

### Procedure

Participation will comprise seven stages:Two-week recruitment and baseline assessment period (see ‘Baseline assessments’ section for details).One-week run-in period. Households will receive a range of differently sized bottled drinks to store in their homes to consume freely. This period functions to acquaint them with both the idea that a wide range of bottle sizes is available and that drinks will be delivered to them over the course of the study. More generally, it will build credibility of the study as a consumer research exercise. Study randomisation will be conducted during this period.First intervention period: 1 week in duration.Second intervention period: 1 week in duration.Third intervention period: 1 week in duration.Fourth intervention period: 1 week in duration.End of study and debriefing.

Stages 1–2 will be completed by any number of eligible households out of the 100 approached that agree to do so.

Stages 3–7 will be completed by 16 households, randomly selected from those completing stages 1–2, who also express a willingness to continue participation in the study. If only 16 households agree to continue their participation, all will be invited to complete these additional stages.

Each household will receive £150 worth of shopping vouchers at the end of the study for completion of all intervention periods and follow-up assessments. This amount was determined based on the national minimum wage rates per hour and the level of commitment and amount of time spent participating in the study (approximately 25 h during 5-week period). Households completing the run-in period but not invited to continue their participation, or not interested in continuing, will receive £30 worth of shopping vouchers.

Households will not be fully informed at recruitment of the purpose of the interventions and of the study’s aim, as it is assumed that such knowledge could potentially influence the outcome. Instead, household representatives will be told that the study involves a consumer research exercise aiming to determine whether and how different bottles affect people’s consumption experiences. Specifically, they will be told that the study will explore whether different bottle sizes influence perceptions of taste, level of enjoyment and satisfaction associated with beverage consumption, perceived product quality and likelihood that the product will be purchased in the future, as well as attitudes towards different bottles, including their appeal and user - friendliness.

### Baseline assessments

At enrolment, household representatives (i.e. individuals who are recruited from each household to provide the necessary data) will be asked to give written informed consent on behalf of their household for participating in the study and for adhering to the study procedures. Following this, they will be requested to complete a questionnaire to record their household’s demographic characteristics, including the number of adults and children living in their home, their age, gender, highest educational qualification and annual household income. They will also be asked to indicate how much cola per week their household usually buys for in-home consumption, as well as the total amount their household drinks outside the home. The amount of cola typically consumed per week by each household will also be estimated based on grocery shopping till receipts, which household representatives will be asked to collect during a 2-week period. Discrepancies between amounts indicated by till receipts and self-report will be discussed with household representatives, in order to determine the household’s typical weekly consumption as accurately as possible.

### Follow-up assessments

At the end of each of the intervention weeks, household representatives will be asked to estimate the amount of SSB their household consumed in the preceding week and to indicate whether any SSB was consumed by non-household members (i.e. visitors). To build credibility for the cover story they will also be asked to rate their consumption experiences, as well as the experience of any visitors they might have had, who consumed part of their SSB stock.

In order to determine whether households believed the cover story or were aware of the purpose of the intervention and of the study’s aim, at the final follow-up assessment, they will be requested to state what they thought the study was about. Awareness of the study’s aim will also be assessed during interviews with household representatives, which will be conducted after the end of all intervention periods. Household representatives will be fully debriefed on the study aims at the end of this final assessment session. The debriefing process will include an explanation of the study’s scientific aim and the reasons for not revealing this at recruitment (i.e. that awareness of the intervention’s purpose was expected to influence the outcome), as well as information regarding the adverse consequences of excessive SSB consumption. This information will be provided both verbally by a member of the research team, as well as in writing. At this point, household representatives will be given the opportunity to make any enquiries regarding the study and address any related issues they might have. They will also be asked to provide written consent for their household’s collected data to be used having been informed of the scientific aims of the study.

### Outcomes and measures

Feasibility outcomesRecruitment ratesNumber of households discontinuing participation at follow-upsAwareness of the study aim, assessed through (i) questionnaire and (ii) qualitative interviewsPractical problems associated with◦The randomisation procedure◦Delivering the intervention◦Collection of consumption-related data

Acceptability outcomes assessed through qualitative interviewsAcceptability of the◦Interventions◦Study procedures◦Assessment procedures

Other outcomes:Characteristics of participating households, assessed through questionnaire◦Index of Multiple Deprivation scores (derived from postcodes)◦Total household income◦Household composition (number of adults; number of children)◦Highest education qualification obtained by any person within the household◦Gender of all household members◦Age of all household membersVolume of cola in millilitres consumed by the household during each of the week-long intervention periods, measuredi.Objectively, by recording the numbers of empty and remaining full bottles. The remaining volume of partly consumed bottles will be weighted and converted to millilitres.ii.Subjectively, through self-report via questionnaire.

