From the above, it is clear that the theoretical literature on this issue is complex and does not allow for confident predictions to be made regarding the impact of bottle size on the consumption of SSBs. However, a large number of studies have examined the effects of portion and package sizing on the consumption of foodstuffs (such as cereal and snack foods) [35–37], and a recent Cochrane review on this topic found that people consume less food the smaller the package size to which they are exposed [38, 39]. It is unclear whether such findings are generalizable to beverage consumption, as there are no studies, to our knowledge, that examine the effects of manipulating the package size of drinks. The lack of relevant studies is also confirmed by the Cochrane review [38, 39]. Based on the aforementioned finding, however, we hypothesise that presenting SSBs in smaller containers will reduce consumption.

To assess this hypothesis and address the absence of relevant evidence, we are proposing a crossover randomised controlled trial to assess the impact of presenting a fixed volume of sugar-sweetened beverages in different bottle sizes on consumption in homes. The focus of this study is on the size of bottles containing cola, given that cola is the most consumed carbonated drink in the UK [8] and is available in a wide range of container sizes. However, prior to conducting this trial, there is a need to reduce key uncertainties related to its design, including the feasibility and acceptability of delivering the intervention to households and replacing existing SSBs and the feasibility of assessing consumption. There are also uncertainties relating to the specific bottle sizes the trial should focus on. As such, we are initially proposing a preliminary study with the aim of assessing the feasibility and acceptability of the procedures for recruitment, allocation, measurement, retention and intervention delivery of the aforementioned randomised controlled trial.

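### The bottle measure records cola that has left the bottle, so cola poured away or spilled counts as consumed and, if waste is greater from large bottles, inflates the size effect

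*Protocol article*

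**What the plan says.** The Outcomes and measures section of the protocol article lists the household's weekly cola volume among the other outcomes and measures it in two ways. The first is: "Objectively, by recording the numbers of empty and remaining full bottles". For bottles that are neither empty nor full, "The remaining volume of partly consumed bottles will be weighted and converted to millilitres" (evidently weighed). The second is: "Subjectively, through self-report via questionnaire".

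The Intervention section supplies the conditions for the count: "households will be requested to continue to keep all bottles whether the contents are consumed, partially consumed or not consumed". Households are told that "the reason for this is to accurately estimate how much they need to pay for their drinks, based on the amount they consumed".

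Under Follow-up assessments, the representative is asked each week to "estimate the amount of SSB their household consumed in the preceding week" and also "to indicate whether any SSB was consumed by non-household members (i.e. visitors"). Ratings of the drinking experience complete the weekly contact as described. No item on cola poured away or spilled is described.

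In the Background the authors state the expected direction: "we hypothesise that presenting SSBs in smaller containers will reduce consumption". The Data analysis section takes the average change from baseline in each intervention period as the source of effect sizes for powering the main trial.

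**The concern.** Delivered volume minus remaining volume equals intake only if nothing leaves the bottle except by being drunk by the household. The protocol recognises one exception, visitors, and asks about it. It describes no question about a second exception, disposal or spillage. An emptied bottle is scored as fully consumed whatever happened to its contents.

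This matters for a comparison of bottle sizes only if the waste depends on size. That is plausible, because the drink is carbonated and a part-used 1500 ml bottle can hold much more to discard than a 250 ml bottle. Waste of that pattern would raise recorded consumption from large bottles and look like the hypothesised effect. The estimate passed to the main trial's sample size calculation would then be too large and the trial too small. Waste that was never recorded cannot be recovered by later analysis. A study whose objectives include the possible effect size and the feasibility of the assessment procedures (Aim and objectives, vii and viii) is the natural place to record it.

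**Working it through.** **Inputs from the protocol article.** Bottle sizes are 250, 500, 1000 and 1500 ml. The weekly delivery is baseline purchase rounded up to a multiple of 3 l (Intervention). The section's examples reproduce: 3 × ceil(2/3) = 3 l, 3 × ceil(3/3) = 3 l, 3 × ceil(3.5/3) = 6 l. A 3 l delivery is 2 × 1500, 3 × 1000, 6 × 500 or 12 × 250 ml. The protocol states no waste rate, effect size, standard deviation or power, so there is no figure of its own to reproduce on this point.

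**Assumed inputs.** True intake T = 2000 ml a week at every bottle size, from a 3000 ml delivery. A share w of the volume that leaves the 1500 ml bottles is discarded, and none from the 250 ml bottles.

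**Step 1: leftovers that stay in the bottle.** Recorded volume R = delivered − remaining. With 1000 ml left and kept, R = 3000 − 1000 = 2000 ml, which equals T. Undrunk cola that is kept causes no error.

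**Step 2: leftovers emptied out.** R = T + waste and waste = w × R, so R = T / (1 − w).

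| w (1500 ml bottles) | R from 1500 ml | R from 250 ml | Spurious difference | As % of R from 1500 ml |
|---|---|---|---|---|
| 0% | 2000 ml | 2000 ml | 0 ml | 0% |
| 2% | 2041 ml | 2000 ml | 41 ml | 2% |
| 5% | 2105 ml | 2000 ml | 105 ml | 5% |
| 10% | 2222 ml | 2000 ml | 222 ml | 10% |

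For a household with a 6 l delivery and T = 4000 ml, the same rates of 2%, 5% and 10% give 82, 211 and 444 ml. The relative difference is unchanged.

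**Step 3: dependence on the assumption.** With waste shares wL (large) and wS (small), the apparent relative reduction is 1 − (1 − wL)/(1 − wS). If wL = wS, including both zero, it is 0. If wL is below wS, the bias runs against the hypothesis.

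**Step 4: scale of one event.** Discarding the last 20% of one 1500 ml bottle is 0.2 × 1500 = 300 ml, or 300/3000 = 10% of a 3 l delivery. The same share of one 250 ml bottle is 50 ml, or 50/3000 = 1.7%.

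**Step 5: route to the main trial.** The effect measure is change from baseline in each period. A household's baseline is the same in all four periods, so it cancels when two sizes are compared, and the spurious difference D enters the contrast in full. At fixed variance and power, sample size varies as 1/Δ². Planning on Δ + D when the truth is Δ gives (Δ/(Δ + D))² of the sample needed. Without a stated Δ this cannot be made a number.

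**The case against.** The case on the other side is substantial.

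- **Kept leftovers are handled.** Households are asked to keep part-consumed and unconsumed bottles, which is most naturally read as keeping them with their contents, and the remainder is measured. Step 1 shows no error here. This stands and narrows the problem to cola emptied or spilled despite the request.
- **Disposal costs money.** A household that empties a bottle is charged for drink it did not have. This stands as a deterrent and gives the household a reason to mention waste, but it leaves no record of the volume.
- **Self-report is a cross-check.** Waste that differed by size should widen the gap between bottle count and self-report for large bottles. This stands in part. One representative estimates for the whole household, so a gap could equally be visitors or recall error. Discussion of discrepancies is described for baseline but not for the intervention weeks.
- **Finding such problems is what the study is for.** Consumption sits under other outcomes, and practical problems in collecting it are a listed feasibility outcome. This lowers the importance and supports asking about waste now.
- **Article-level detail.** The full weekly form and household instructions are not shown and may include a discard item. That is fair. The point rests on the stated definition of the measure and on the items the article does name.

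A reader might go further and infer that flat leftovers from large bottles are generally scored as consumed, so that the measure by its nature imitates the hypothesised effect. The documents do not support that. They provide for keeping and measuring leftovers, and they say nothing about cola going flat, being poured away, or waste differing by size.

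**Conclusion.** The point holds in a limited form. As defined, the objective measure cannot separate drinking from disposal or spillage, and the weekly assessment as described does not record either. Any waste that rises with bottle size would bias the size contrast towards the hypothesis and pass into the effect size for the main trial.

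The size is conditional: about 41-222 ml a week (2-10%) at 2 l true intake, if 2-10% of what leaves 1500 ml bottles is wasted and nothing from 250 ml bottles. Both the rates and the dependence on size are assumptions. With no waste, or equal waste, the relative difference is unbiased. It would also be a mistake to infer that the main trial is bound to inherit the error, because the protocol treats the assessment of consumption as still open. This is an inexpensive improvement to a secondary measure and does not invalidate the study.

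**What to change.** 1. **Intervention section.** Add to the bottle-keeping request that any undrunk cola should be left in its bottle. This fits the reason already given to households and needs no change to the cover story.
2. **Follow-up assessments section.** Next to the visitor question, add one weekly item on the approximate volume of delivered cola poured away or spilled.
3. **Outcomes and measures section.** Keep the objective measure as delivered volume, including additional deliveries, minus remaining volume. Tabulate reported discards by bottle size. Report consumption net of reported discards as a sensitivity analysis beside the unadjusted effect size.

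The reported discards should not be subtracted inside the objective measure itself, because that would mix recall into the only measure that is free of it.

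The cost is one sentence of instruction and one item on an existing weekly contact. The item is self-reported and subject to recall error. Because households pay by amount consumed, the form should also make clear whether a reported discard affects the charge, since otherwise answers may be slanted.
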